#### Serious adverse events (SAEs)

Expected SAEs that are a more common occurrence in this study population are self-harm leading to hospitalisation; suicidal attempts leading to hospitalisation; worsening of depression leading to hospitalisation. These expected SAEs will still be reported. Admission to hospital for pre-planned surgery for pre-existing conditions will not be reported as an SAE.

All AEs and SAEs will be assessed by a clinical PI or nominated deputy clinician. We will develop a detailed, SOP for reporting and recording AEs. The Data Monitoring and Ethics Committee (DMEC) will periodically review overall safety data to determine patterns and trends of events, or to identify safety issues, which would not be apparent on an individual case-by-case basis.

Adverse events/reactions will be recorded and reported from the point of consent (baseline assessment) until the 12-month follow-up assessment or point of withdrawal from the study.

### Statistical considerations

#### Outcome measures

##### Primary outcome

The primary outcome will be the score on the Beck Depression Inventory (BDI-II) at 6 months post-randomisation, measured as a continuous variable.

##### Secondary outcomes

Secondary outcomes will include response (at least 50% reduction in depressive symptoms on the BDI-II compared with baseline), remission of symptoms (BDI-II < 10), percentage reduction in depressive symptoms on the BDI-II, depressive symptoms on the PHQ-9, quality of life (EQ-5D-5L and WSAS), and anxiety (GAD-7), all measured at 6 months post-randomisation, together with these outcomes and the continuous score on the BDI-II (primary outcome) measured at 12 months post-randomisation. Data on the PHQ-9 and GAD-7 were also collected as part of the brief telephone follow-ups at 3- and 9-months.

In addition, the EQ-5D-5L will inform the economic evaluation, as will data on the use of primary care consultations and prescribed medication collected from practice medical records. Data on the use of other primary and community care services; secondary care related to mental health, private treatments, use of social services, burden on informal caregivers, personal costs related to mental health and benefits received will also inform the economic evaluation.

#### Justification of sample size

The NICE depression guidelines group [50] suggested that 0.35SD represents a clinically important difference on our primary outcome, which is approximately 4–5 points on the BDI-II (IPCRESS/CoBalT: standard deviation 12.9/13.9). On this basis, 173 participants in each group give 90% power to detect a difference of 0.35 standard deviations on the BDI-II at a two-sided 5% significance level. Assuming 20% attrition at 6 months, we need to recruit 434 patients.

However, given that referral to IAPT may be part of usual care for the comparator group, it is possible that this may affect the plausibility of the target difference between groups. While it is difficult to determine the impact of this, if the difference to be detected was reduced to 0.30 SD and we achieve a slightly higher follow-up rate (85%) in line with previous trials [8], with a total sample size of 434 patients, we would still have adequate (> 80%) power to detect such a difference (see Table 2 below).

**Table 2 Tab2:** Sensitivity of sample size calculation to changes in plausible target difference between groups and variations in required power and attrition at 6 months

	**Power**	**80% power**		**90% power**	
	Attrition at 6 months	15%	20%	15%	20%
**Difference to be detected**	0.35 SD	306	326	408	434
	0.30 SD	414	440	554	588

We have not inflated our sample size to account for clustering by therapist as there was little evidence of any therapist effects in our previous trials of CBT for depression [2, 8]. The intraclass correlation coefficients for the continuous BDI outcome (adjusted for baseline BDI score) were very small for CoBalT (0.0027) and for IPCRESS, its precise value could not be estimated indicating it was almost zero. Hence, inflating the sample size to account for any potential clustering by therapist would be unduly conservative. Nevertheless, we will use established methods [51] to obtain a fully heteroscedastic model to explore any potential therapist effects in secondary analyses.

#### Internal pilot

There will be a 9-month internal pilot to ensure that we are able to recruit to the main trial as planned and that participants are engaging with the intervention as expected.

#### Criteria to judge success of internal pilot

Our progression criteria are that, by the end of the internal pilot phase, we will have achieved:At least 70% of our anticipated recruitment rate (8 patients per month) in the Bristol site;At least 70% of those randomised in the Bristol site will have received at least two sessions with a therapist; andRecruitment will have commenced at the other sites (London and Hull/York). (London and Hull/York will commence set-up four months after the Bristol site.)

We will employ a traffic-light system to judge the success of our internal pilot. If we achieve at least 70% of our target for recruitment and engagement with the intervention and have commenced recruitment at other sites, then we will continue the study. However, if appropriate, we will explore the reasons for not achieving the target and whether any modifications to recruitment processes are required dependent on the emerging recruitment rate trajectory. If we achieve between 50 and 70% of our recruitment and engagement targets, and/or have not commenced recruitment at other sites, then we will discuss with our Trial Steering Committee whether we should make changes to the recruitment/therapy processes and whether we should continue. If we recruit less than 50% of our recruitment and engagement targets and have not commenced recruitment in other sites, then we would stop the trial. We believe that these progression criteria are realistic based on our experience and account for the fact that recruitment builds over the early months of a trial.

The criteria to judge success were informed by guidance published by Avery et al. [52] and account for the fact that two recruiting sites (London and Hull/York) will have had only a short period to commence recruitment. The second target is based on data from our previous CBT trials [2, 8] in which 9–13% of those randomised to receive the intervention did not attend any sessions and a further 3–7% of participants only attended one session with a therapist, giving an overall percentage of 12–19% attending fewer than two sessions.

### Statistical analysis

Analysis and reporting will be in line with CONSORT guidelines [53]. A detailed statistical analysis plan will be prepared and approval sought from the Trial Steering Committee prior to data lock. The analysis plan will be published on the University of Bristol Research Portal. A brief outline of the proposed analysis is presented below.

All analyses will be conducted according to the intention-to-treat principle. Descriptive statistics will be used to ascertain any marked imbalances in demographic or clinical variables at baseline.

Analysis of the primary outcome will use linear regression to compare the groups as randomised, adjusting for stratification/minimisation variables and baseline measurement of the outcome. Analyses of continuous secondary outcomes will be conducted in the same manner as the primary outcome and binary secondary outcomes will be analysed using logistic regression adjusting for stratification/minimisation variables. We will undertake exploratory analyses using regression methods to examine the impact of process measures such as the extent of involvement in CBT/other interventions (including the use of the INTERACT platform), use of online materials, and therapeutic alliance [43].

In all analyses, we will present regression coefficients (for continuous outcomes) or odds ratios (OR) (for binary outcomes), with 95% confidence intervals and p values. Repeated measures analyses will incorporate outcomes over the 12 months. An interaction between the treatment group and time will formally assess whether treatment effects are sustained or emerge later. We will conduct sensitivity analyses to examine the impact of missing data, baseline imbalances in important prognostic factors, number of treatment sessions attended, potential “therapist effects” and the timing of questionnaire completion. Recognising the inherent biases in per-protocol analyses, a Complier Average Causal Effect (CACE) analysis is planned to estimate the treatment effect among compliers who attended an adequate number of CBT sessions. Sub-group analyses will explore the possibility of differential treatment effects based on the chronicity and severity of depression, and personality difficulties [36].

No planned interim analysis of outcome data will be conducted.

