### Randomisation

Randomisation will be stratified by centre and minimised on gender (male/female), current antidepressant use (yes/no), and depression severity using BDI-II tertiles derived from the CoBalT study [2, 39] baseline scores (BDI-II ≤ 25; 26–35; ≥ 36). If participants indicate a non-binary gender at baseline, we will use an unpredictable computer-generated code to randomly select a binary gender code, prior to randomising them to a treatment group in the usual way. (Details of self-reported gender will be given in full as part of the reporting process.) We will use minimisation with a probability weighting of 0.8 to reduce predictability [40]. Stratifying by centre will ensure a balance in terms of local differences and also proportionate workload for therapists. The minimisation variables are important prognostic indicators on which we wish to ensure a balance between the two groups.

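### The logistic models for response and remission list no continuous baseline BDI-II score, although the primary model does; adding it is a small, free gain, almost all of it for remission

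*Protocol article*

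**What the plan says.** All references are to the Protocol article.

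- **Statistical analysis, primary outcome:** linear regression, "adjusting for stratification/minimisation variables and baseline measurement of the outcome".
- **Statistical analysis, continuous secondary outcomes:** "Analyses of continuous secondary outcomes will be conducted in the same manner as the primary outcome".
- **Statistical analysis, binary secondary outcomes:** "binary secondary outcomes will be analysed using logistic regression adjusting for stratification/minimisation variables". No baseline score is named.
- **Randomisation:** centre is the stratification factor. The minimisation factors are gender, current antidepressant use and "depression severity using BDI-II tertiles derived from the CoBalT study", with bands of 25 or below, 26 to 35, and 36 or above.
- **Secondary outcomes:** the two binary outcomes both come from the BDI-II, at 6 and 12 months. Response is "at least 50% reduction in depressive symptoms on the BDI-II compared with baseline". Remission is an absolute threshold, "remission of symptoms (BDI-II < 10").

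The exact BDI-II score is recorded for everyone at the baseline assessment, since entry requires 14 or more.

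**The concern.** Adjacent sentences set different covariate lists for outcomes taken from the same questionnaire. The primary BDI-II analysis uses the baseline score as well as the randomisation factors. The response and remission analyses list the randomisation factors only, and the document defines severity among those factors only as a band.

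The bands are wide. With entry at 14, the lowest runs from 14 to 25; the highest has no stated upper limit. Remission is a fixed cut-off, so within a band a participant who starts lower has less far to go. A model with the band alone treats everyone in a band as having the same starting severity.

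Two modest things are at stake. One is precision for remission. The other is the meaning of the reported odds ratio: odds ratios are non-collapsible, so the covariate set partly defines the quantity being estimated and is best settled before the data are seen.

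**Working it through.** **1. The plan's own figure.** No power or sample size is stated for response or remission. The figure for the primary outcome does reproduce. Normal approximation: n per group = 2(1.960 + 1.282)²/0.35² = 171.6, so 172. The t-test version gives 172.5, so 173 as stated. Attrition of 20%: 173/0.8 = 216.25, so 217 per arm and 434 in total. Hence 2 × 173 = 346 analysed is used below.

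**2. Why the band is not the whole story for remission.** Assume a usual-care mean of 22 at 6 months for a baseline of 31, a slope of 0.7 on baseline and a residual SD of 11 (none of these is in the document). Expected 6-month scores at the two ends of the lowest band:

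- baseline 14: 22 + 0.7 × (14 − 31) = 10.1
- baseline 25: 22 + 0.7 × (25 − 31) = 17.8

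The score is a whole number, so remission means below 9.5 on the continuous scale. P(Z < (9.5 − 10.1)/11) is about 48%, and P(Z < (9.5 − 17.8)/11) is about 23%. The gradient applies to both arms alike. It shows prognostic information inside a band, not bias.

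**3. What the continuous score adds.** 2,000 trials were simulated per scenario.

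- From the document: 346 analysed, 1:1 allocation, effect 0.35 SD, two-sided 5% test, SD 13.4 (midway between the stated 12.9 and 13.9), the three bands, and the definitions of response and remission.
- Assumed: baseline BDI-II roughly normal with mean 30.5 and SD 10.5, limited to 14 to 63; usual-care mean 22 at 6 months; baseline-to-outcome correlation as tabulated.
- Centre, gender and antidepressant use were left out.

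Overall remission came out at about 23% and response at about 38 to 39%. The bands explained about 82% of the variance in baseline score, leaving about 18% for the continuous term to recover.

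| Correlation | Remission power: band, then band + score | Response power: band, then band + score |
|---|---|---|
| 0.3 | 66.0%, 65.8% | 77.2%, 77.2% |
| 0.4 | 68.2%, 68.8% | 79.2%, 79.1% |
| 0.5 | 70.2%, 71.1% | 83.4%, 83.4% |
| 0.6 | 72.4%, 74.2% | 86.8%, 87.4% |

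**4. As effective sample size for remission.** Take the squared ratio of (mean log odds ratio / mean standard error) between the two models:

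- correlation 0.3: (0.647/0.273)² ÷ (0.642/0.272)² = 1.008
- correlation 0.5: (0.711/0.286)² ÷ (0.695/0.281)² = 1.010
- correlation 0.6: (0.765/0.297)² ÷ (0.732/0.290)² = 1.041

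A separate simulation extended to correlation 0.7 gave about 1 to 5% for effective sample size and 0.5 to 2.3 points of power for remission, with almost nothing for response. On 346 analysed, 1 to 5% is about 3 to 17 participants.

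**5. Simulation noise.** If the 5% verdict differs between the two models in about 3 to 5% of trials, as a further simulation under similar assumptions found, the standard error of a paired power difference over 2,000 trials is about √(0.03/2000) to √(0.05/2000), or 0.4 to 0.5 points. The −0.2 at correlation 0.3 is therefore compatible with a gain of half a point.

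**6. The estimand.** At correlation 0.5 the mean log odds ratio for remission moves from 0.695 to 0.711, that is, an odds ratio of 2.00 against 2.04. The shift is small, but it follows from the covariate list alone.

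**The case against.** The strongest reply is that nothing here is an error. Logistic regression adjusted for the randomisation factors is a standard and valid randomised comparison. The article calls its analysis text a brief outline and promises a detailed analysis plan before data lock, and it does not say in what form severity enters the model. The phrase about the baseline measurement of the outcome also has no direct counterpart for the binary outcomes: nobody who enters with a BDI-II of 14 or more is in remission at baseline, and response is already defined against each participant's own baseline.

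Most of this stands, and it is why the point is minor. What remains is that the article names the covariates for the binary outcomes, leaves the baseline score off that list, and defines severity elsewhere only as a band. An analysis plan that follows the text would carry the omission forward.

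Three stronger readings are tempting, and the document supports none of them.

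- **That baseline information is thrown away.** Under the stated assumptions the bands keep about 82% of the baseline variance.
- **That every continuous outcome is adjusted for its own baseline.** The list includes "percentage reduction in depressive symptoms on the BDI-II, depressive symptoms on the PHQ-9", and percentage reduction has no baseline value of its own.
- **That drop-out related to severity will bias the odds ratios.** The article does not specify a complete-case analysis for these outcomes, and no such bias has been quantified. It also plans sensitivity analyses for missing data and for baseline imbalance in prognostic factors, though without naming covariates or outcomes for them.

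**Conclusion.** The difference in covariate lists is real, and its consequence is small. It leaves some already collected baseline information unused for remission, worth about 1 to 5% in effective sample size and about 0.5 to 2 points of power. For response the gain is close to nil. The analysis as written is valid, the primary outcome is unaffected and the sample size of 434 does not change. This is an optional improvement, not a correction.

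The size rests on assumptions from outside the document: the baseline distribution, the usual-care mean at 6 months and a baseline-to-outcome correlation of 0.3 to 0.7. The gain is largest at the top of that range. It also takes severity to enter the logistic model as the band, the only form the article defines. If the continuous score was always intended, the remedy is simply to say so.

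**What to change.** Extend the sentence for binary outcomes so that, after "binary secondary outcomes will be analysed using logistic regression adjusting for stratification/minimisation variables", it continues: and continuous baseline BDI-II score, at 6 and 12 months. If the score is left out on purpose, the analysis plan should say why. Either way, the covariate set should be fixed before data lock.

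The cost is one clause and one extra term in each model. No new data are needed, and neither the primary analysis nor the sample size changes.

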### Economic evaluation

#### Perspectives

An economic evaluation alongside the RCT will estimate the incremental cost-effectiveness of the integrated approach to delivering CBT over and above usual care. The evaluation will be conducted from three perspectives: (1) the National Health Service and personal social services; (2) patients and informal carers; and (3) society.

#### Outcomes

Resource use data will be collected from three sources: (1) trial records, resources used to deliver the intervention will be recorded throughout the trial; (2) General Practice records—primary care consultations and prescribed medication will be extracted for the 12-month trial period; (3) resource use questionnaire will be administered at 6 and 12 months providing information on the use of hospital and community services; specialist mental health contacts; private treatments; use of social services; burden on informal caregivers; personal costs (e.g. time off work/unpaid activities); and benefits received. Total staff costs to deliver the intervention will be valued assuming mid-point salaries plus salary on-costs. Recognised published sources, such as (Personal Social Services Research Unit Costs of Health and Social Care, National Cost Collection, Prescription Cost Analysis, Labour Market Data by Office for National Statistics, etc.) will be used to apply national average unit costs to service utilisation and construct a cost profile for each patient in the trial.

For outcomes relevant to national policy, cost-utility analysis as recommended by NICE Guidance [54], will examine incremental quality-adjusted life years (QALYs), by collecting information on generic health using the EQ-5D-5L at baseline, 6 and 12 months and calculating the area under the curve [55]. We will use the 5L version of the EQ-5D and the tariff recommended by the latest NICE guidance at the time of analysis. NICE currently recommends the use of the 3L tariff [56], but should any further guidance be subsequently issued we will adhere to that.

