### Trial intervention — integrated cognitive behavioural therapy for depression

The intervention is provided individually and comprises nine therapist-led sessions, with (up to) a further three sessions if deemed clinically appropriate by the therapist. The first session will last 60–90 min and take place face-face via videocall (independent of the INTERACT platform), with subsequent 50-min sessions taking place online using the INTERACT therapy platform, via instant messaging/typing. Patients in the intervention arm will also continue to be cared for as usual by their GP.

The INTERACT protocol utilises the standard Beckian intervention for depression [44-46]. In considering the detailed content of Beck’s intervention for depression, we refer to the UCL competence framework for CBT [47] and the problem-specific competences [48].

To ensure that the results of the trial apply to standard clinical settings, we will recruit CBT practitioners comparable to those working as high-intensity therapists within IAPT services. Hence, therapists will be mental health professionals with appropriate post-qualification CBT training (British Association for Behavioural and Cognitive Psychotherapies (BABCP) accreditation) or equivalent experience. All therapists will be employed by the study or seconded to the study from local NHS Trusts/Psychological Services, for the duration of the study. Therapists will start 1 month before the start of delivery of therapy in order for them to receive training in the use of the platform and study procedures, and to enable them to familiarise themselves with the range of resources available. During the study, therapists will receive weekly supervision from an experienced therapist. This arrangement mimics local NHS practice and meets the standards for clinical supervision set out by the BABCP. Therapists will be provided with detailed training manuals and SOPs, e.g. for risk assessment and management.

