### Trial comparator — usual care

Participants allocated usual care will continue to receive treatment as usual from their GP. This is not standardised and may include referral to local psychological services provided by IAPT or antidepressant medication, as appropriate. There will be no restrictions on the treatment options that can be offered to this group. However, we will record receipt of psychological therapy received through IAPT or privately as part of the follow-up questionnaires (in addition to other data on treatments and health care usage during the trial).

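### Trial therapy and comparable therapy in usual care are priced on different bases, which would understate incremental cost if only the service prices carry overheads

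*Protocol article*

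**What the plan says.** The Outcomes part of the Economic evaluation section of the protocol article names the sources of resource-use data and then how they are priced. For the intervention, the source is "trial records, resources used to deliver the intervention will be recorded throughout the trial". The pricing rule for staff is "Total staff costs to deliver the intervention will be valued assuming mid-point salaries plus salary on-costs". For the care that patients use, recognised published cost sources "will be used to apply national average unit costs to service utilisation and construct a cost profile for each patient in the trial". The resource-use questionnaire covers, among other items, "specialist mental health contacts; private treatments; use of social services".

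Two other sections make trial therapy and outside therapy alike. Under the trial comparator, usual care "may include referral to local psychological services provided by IAPT or antidepressant medication, as appropriate", and "we will record receipt of psychological therapy received through IAPT or privately as part of the follow-up questionnaires". Under the trial intervention, "we will recruit CBT practitioners comparable to those working as high-intensity therapists within IAPT services". The intervention "comprises nine therapist-led sessions, with (up to) a further three sessions if deemed clinically appropriate by the therapist".

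The Analysis part of the Economic evaluation section refers to a separate health economic analysis plan, to be made public before data lock. It also plans sensitivity analyses on unit cost estimates.

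**The concern.** Followed literally, these rules can give an hour of similar therapy a pay-based price when the trial delivers it and a service-based price when IAPT delivers it. If the service price contains overheads such as premises, management and IT, and the trial price does not, the two arms are not costed alike.

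Cost-effectiveness is one of the two main objectives, and the first perspective is that of the NHS and personal social services. The article says that the model could be introduced into existing psychological services; a commissioner doing so would bear the cost of running a service as well as pay. An understated intervention cost lowers incremental cost, raises net benefit and moves the acceptability curve towards integrated CBT. Because the error would be systematic, a larger sample would not reduce it.

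**Working it through.** The article states no wage, unit cost, overhead rate or incremental cost, so there is no figure of its own to reproduce. The check is algebraic, with an assumed range for the one unknown.

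**Inputs**
- S: intervention staff cost per participant at mid-point salary plus on-costs (Economic evaluation, Outcomes). Indexed at 100.
- h: overhead share carried by national unit costs and absent from salary plus on-costs. Not given in the documents; assumed 0 to 0.75.
- v: net excess of outside therapy in the usual-care arm over the intervention arm, as a share of the intervention's therapy volume. Not given; assumed 0 and 0.5.
- Staff time is counted in the same way on both bases.

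**Incremental therapy cost**
- One basis, full cost for both: S(1+h) − S(1+h)v = S(1+h)(1−v).
- Mixed basis, as the text reads: S − S(1+h)v.
- Difference: S(1+h) − S = hS. The term in v cancels, so the absolute understatement does not depend on how much outside therapy usual-care patients receive.

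**Results with S = 100**

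| h (assumed) | Understatement hS | Share of full-cost incremental therapy cost, v = 0 | Same, v = 0.5 |
|---|---|---|---|
| 0 | 0 | 0% | 0% |
| 0.10 | 10 | 9% | 18% |
| 0.25 | 25 | 20% | 40% |
| 0.50 | 50 | 33% | 67% |
| 0.75 | 75 | 43% | 86% |

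Each share is h / [(1+h)(1−v)]; for example, 0.25 / (1.25 × 0.5) = 0.40.

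**Therapist time exposed to the price difference.** The intervention section gives a first session of 60–90 minutes and later sessions of 50 minutes.
- Nine sessions: (60 to 90) + 8 × 50 = 460–490 minutes, or 7.7–8.2 hours.
- Twelve sessions: (60 to 90) + 11 × 50 = 610–640 minutes, or 10.2–10.7 hours.

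Each GBP 1 per contact hour between the two price bases is therefore worth GBP 7.7–8.2 for a patient who completes nine sessions and GBP 10.2–10.7 for one who completes twelve. The intention-to-treat mean would be lower if attendance falls short of nine: therapy may end by agreement before then, and the internal pilot section reports that 12–19% attended fewer than two sessions in earlier trials. The documents do not give the hourly difference, so the calculation stops here.

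**The case against.** The strongest reply is that a condensed article is being read as a full costing rule. Several parts of that reply stand.

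- The pay-based sentence covers staff costs only and includes on-costs, so calling it bare pay would be wrong.
- It refers to total staff costs, not contact hours. Therapists are employed or seconded for the whole study, trained for a month beforehand and supervised weekly. If all that paid time is counted, non-contact time may already be included, and trial therapy could even cost more per contact hour than a service rate. Overheads are the firmer part of the point.
- Resources used to deliver the intervention are recorded separately, and nothing says that overheads or platform costs are left out.
- The price for IAPT or private therapy is not named, and the article does not say that the published unit costs contain overheads.

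A reader might infer that the incremental cost is already biased, or that all other care is priced at full cost. The text supports neither reading.

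Two parts of the reply do not dispose of the point. The health economic analysis plan may settle the detail, but the article already fixes a staff valuation rule: a plan that follows it without adding overheads keeps the two bases, and one that departs from it needs the article clarified. The planned sensitivity analyses address uncertainty in unit costs; they do not commit to a common basis for like therapy, and they would not correct the base case.

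**Conclusion.** The point holds as a conditional one. The article names different price bases for trial staff and for service use, and by its own account the second can include therapy comparable to the trial's. If the national unit costs carry overheads, none are added to trial staff costs, and staff time is counted alike on both bases, incremental cost is understated by h times the intervention staff cost, in favour of integrated CBT. With h = 0 there is no understatement.

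The direction follows from those conditions; the size does not follow from the documents. The percentages above show sensitivity to an assumed h and are not estimates. Any GBP or QALY figure would be illustrative only. It would be too strong to say that the economic result will be biased, because the health economic analysis plan is not shown and may already add what is missing.

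**What to change.** In the Outcomes text of the economic evaluation, and in the health economic analysis plan, state that trial therapist and supervisor time and comparable outside therapy are on one price basis in the base case. Either route works:

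1. Add overheads suited to remote delivery to salary plus on-costs, together with a per-patient share of platform running costs if these are not already costed under the recorded intervention resources.
2. Apply the same published full hourly unit cost to trial therapy and to comparable outside therapy, taking care not to count non-contact time twice.

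Report salary plus on-costs alone as a sensitivity analysis. The change is to wording and unit prices and needs no new patient data. The downside is that the cost-effectiveness result may become slightly less favourable to integrated CBT.
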